## 2.2 Background

### 2.2.1 HPV epidemiology

At least 610,000 cancer cases are attributed annually to high-risk Human Papillomavirus (HPV) infections, including all cervical cancers and a significant proportion of ano-genital (vulvar, vagina, penile, and anal) and oropharyngeal cancers. Cervical cancer affects women in the prime of life, at a time when they are raising and caring for families and contributing socially and economically to their communities, therefore the development of new strategies for cervical cancer prevention is undoubtedly a priority area for the improvement of women's health that could generate a strong economic and social impact on the world population.

Understanding the role of HPV in cervical cancer (the third most common cancer in women worldwide, producing more than 310.000 annual deaths) has promoted the development of two major cancer prevention strategies: primary prevention through prophylactic HPV vaccination, and secondary prevention based on the detection of HPV infection and treatable pre-cancers and early cancers.

On May 19th, 2018 the World Health Organization's Director-General made a global call for action towards the elimination of cervical cancer. In response to this call, the governments of many countries are now interested in identifying the best strategy to combine vaccination and screening and obtain the best cost-benefit balance.

### 2.2.2 HPV viral cycle

More than 200 human papillomaviruses have been described until now, but only a limited group of 12 genotypes (16, 18, 31, 33, 35, 39, 45, 51, 52, 56, 58 and 59), showing carcinogenic capacity, have been classified by the IARC as high-risk HPV types (HR-HPV). HPV16 is the most carcinogenic type and is detected in more than 70% of cervical cancers. Despite being a heterogeneous group of viruses, the genome structure and associated carcinogenic process for all HR-HPV is similar. A circular double-stranded DNA genome encodes the capsid proteins (L1 and L2), which are crucial for the first steps of binding and viral entry and are also important to

generate a type-specific immune response. Initial HPV16 binding occurs via heparan-sulphate proteoglycans (HSPGs) located on the epithelial cells. Cyclophilin B mediates the conformational change in the virus capsid that increases the exposure of the N-terminus of L2 protein and facilitates efficient infection. HPV16 genome also encodes a group of early proteins named E1, E2, E4, E5, E6, and E7. E1, E2 and E4 are essential to maintain the viral fitness (replication, virion synthesis and release). E1E4 fusion protein is the most highly expressed protein in the productive life cycle of human papillomaviruses; it contributes to multiple facets of the virus life cycle and may facilitate efficient virus release and transmission. E6 and E7 (and partially E5) are mainly involved in the carcinogenic process.

### 2.2.3 HPV prophylactic vaccines, viral entry and antibody neutralization

Prophylactic vaccines are based on the expression of recombinant L1 protein subunits that can self-assemble generating virus-like particles (VLPs), with type-specific conformation, which mimics morphological and immunological characteristics of native virions. L1 VLPs-based vaccines have demonstrated a high degree of safety, immunogenicity and effectiveness, preventing HPV infection and malignant lesions caused by the targeted genotypes.

9vHPV (Gardasil-9™, manufactured by MSD) protects against 9 genotypes (HPV 6, 11, 16, 18, 31, 33, 45, 52, and 58) that together are responsible for 90% of cervical cancer cases. It was originally licensed as a 3-dose regimen, which is the regimen adopted for this study. It contains amorphous aluminium hydroxyphosphate sulphate as adjuvant.

Although the mechanism of protection is not fully understood, is largely accepted that neutralizing antibodies (nAbs) play a crucial role preventing virus particle binding to the epithelial cell surface and inhibiting viral entry. The available data suggest that nAbs can block early extracellular events preventing the interaction between L1 and heparin sulphate proteoglycans on the basement membrane. nAbs can also block those binding effects that occur before and after changes in L2 protein. An alternative post-entry nAbs mechanism that involves the activation of TRIM21 pathway has been described in a wide range of non-enveloped virus. TRIM21, which resides in the cytoplasm, targets the viral nAbs- labelled particles for proteasomal degradation after completing the entry.

Regardless of the specific mechanism of neutralization, nAbs produced after vaccination confer a long period of individual protection against a new HPV infection, which is much more effective than a natural serological response. HPV vaccines have shown high efficacy, immunogenicity, and safety also in individuals previously exposed to HPV. However, L1-VLP vaccines are prophylactic, not therapeutic: once the HPV infection is present, nAbs generated in response to vaccination can prevent new infections, but cannot eliminate the virus-infected cells. It is for this reason that most HPV vaccination programs are aimed at adolescents before the first sexual encounter occurs. Little is known about the effect of vaccination in the transmission of HPV infection between sexual partners.

#### 2.2.4 Antibody and viral particle detection in body fluids and models to assess viral infectivity

Previous studies have shown that anti-L1 antibodies are present in cervicovaginal and oral fluids in vaccinated women, in asymptomatic men or women with a positive serology for HPV16, and in oral mucosal transudates from HIV/HPV-positive individuals.

Vaccine-induced HPV antibodies originating from cervicovaginal secretions have also recently detected in first-void (FV) urine. Discharged mucus and debris from exfoliated cells from the female genital organs accumulate around the urethra opening, between the small labia, and are washed away mainly with the urine initial flow (first-void urine).

Moreover, new viral particles are present in body fluids obtained from individuals showing a productive HPV infection and HPV DNA has been detected in first-void urine. Although the direct interaction between antibodies and viral particles has not been demonstrated so far in the same group of HPV-positive individuals, the simultaneous detection of viral particles and anti-L1 antibodies in cervical, anal, vulvar and oral fluids suggest that anti-L1 antibodies, despite being unable to suppress the production and release of new viral particles, could decorate the viral capsid and limit their infectivity. As the vaccine VLPs induce a higher antibody response compared to natural serological responses, it could be expected that the interaction between anti-L1 antibodies and new produced viral particles, and therefore, viral neutralization, will be more effective in vaccinated women. In line with this, an evaluation of HPV transmission among heterosexual couples in the HITCH prospective cohort yielded a reduced transmission associated to vaccinated women, and a currently ongoing clinical trial is evaluating the effect of vaccination on the reduction of HPV DNA positivity incidence in sexually active couples ([NCT01824537](#)). However, new assays to functionally assess the reduction of infective capacity are indispensable to distinguish the effect of the vaccine on the prevention of new infections, from the effect on the infective capacity and transmission of HPV infections already present before vaccination.

Serology techniques based on neutralization assays, competitive immunoassays and ELISA have been used to evaluate antibody response to HPV vaccines. Although neutralization assays mimic functions closest to the natural mechanisms, they require cell culture and are time-consuming. ELISA assays are fast and easy to multiplex, but they detect neutralizing and non-neutralizing antibodies. In HPV-positive, individuals that have been vaccinated (immunocompromised individuals or post-treatment vaccination) serology assays are unable to distinguish antibodies produced as a natural response to viral particles from the antibodies induced after vaccination.

Because HPV life cycle is dependent on the differentiation of basal cells into keratinocytes, it is challenging to study *in vitro*. 3D organotypic raft culture systems that mimic epithelial cell differentiation *in vitro* have been used to produce virions with infectious potential. However, 3D cultures are usually complex to standardize and replicate, what make them inefficient for large-scale epidemiologic studies or clinical trials. Although HPV cannot complete the viral cycle in a 2D cell culture, 2D models are easy to standardize and have emerged as useful tools for analyzing the first steps associated with viral binding, cell-entry and infection. Ozbun and co-workers developed a model to analyze the HPV infective capacity based on the culture of HaCaT

keratinocytes. HaCaT cells are incubated with biological samples potentially containing viral particles and after 24-48 hours the expression of the E1E4 mRNA is used to quantify the number of cells that have been infected. E1E4 mRNA expression is essential to maintain viral fitness and complete the viral cycle and is used as a surrogate marker that indicates infection of epithelial cells and activation of the viral replication machinery. Differences in E1E4 activity impacts several processes such as viral capsid assembly, maturation and infectivity. This functional assay can quantify infectious particles present in the sample, through the quantification of cells expressing E1E4 mRNA. In the present study, we will evaluate two different protocols (see section 8.2.2) to analyze the expression of E1E4 mRNA in HaCaT cells exposed to cervical, anal, urine, vulvar or oral samples with the aim of developing a standardized and reproducible protocol for the development of larger clinical trials in women and men.

### 2.2.5 Pharmaceutical and Therapeutic Background

The 9vHPV vaccine (Gardasil-9™) is an aluminium-adjuvanted recombinant protein vaccine prepared from the highly purified VLPs of the recombinant major capsid (L1) protein of HPV Types 6, 11, 16, 18, 31, 33, 45, 52, and 58.

The 9vHPV vaccine is currently indicated by the European Medicines Agency (EMA) in males and females from the age of nine years for the prevention of dysplastic lesions and cancers of the cervix, vagina, vulva, and anus, as well as for prevention of genital warts caused by the HPV types targeted by the vaccine.

According to the US Food and Drug Administration (FDA), the 9vHPV vaccine is indicated in males and females 9 through 45 years of age for the prevention of the following diseases caused by the vaccine-targeted HPV types: intraepithelial neoplasia of the cervix, vagina, vulva and anus, genital warts and cervical adenocarcinoma in situ. In males 9 through 45 years of age, it is also indicated for the prevention of anal, oropharyngeal and other head and neck cancers caused by the vaccine-targeted HPV types.

### 2.2.6 Clinical and Population-Based Studies

Safety of HPV vaccines has been ascertained through evaluation of surveillance data obtained from more than 270 million doses administered in immunization programs, showing no association with serious adverse events.

Efficacy of HPV vaccines in clinical trials is ~100% in a three-dose regimen in HPV-negative women younger than 25 years of age, for protection against cervical persistent infection and cervical pre-cancerous lesions, and sustained protection has been demonstrated for up to 12 years of follow-up in several population-based studies. Protection against cervical pre-cancerous lesions in older women (24 to 45 years) has also been demonstrated, although efficacy is lower compared to younger women.

Results from a recent population-based study in Sweden showed a ~90% reduction in cervical cancer incidence in vaccinated women younger than 17 years of age. The same study showed a lower but robust reduction (53%) in cervical cancer incidence in women vaccinated at 17 to 30 years of age.

A recent meta-analysis including randomized clinical trials and several retrospective, prospective and cancer registry studies showed a significant risk reduction of new cervical pre-cancerous lesions after cervical excision in women vaccinated at a time close to surgery. Results of this meta-analysis demonstrated no difference in risk reduction between women younger than 25 years and older women, and are thus an additional argument in favour of vaccination of HPV-positive older women.

Regarding HPV transmission reduction and prevention, analysis of data from a prospective cohort study of heterosexual couples (HITCH) yielded a reduction in HPV transmission to their male partners from vaccinated women compared to couples with unvaccinated women, and those vaccinated women with infections of HPV types covered by the vaccine (acquired prior to vaccination) had lower viral loads than unvaccinated women. Also, the currently ongoing TRAP-HPV study will evaluate the effect of vaccination on the reduction of HPV DNA positivity incidence in sexually active couples ([NCT01824537](#)). This study is phase 4, interventional, randomized to receive 9vHPV vaccine or a placebo (Hepatitis A vaccine), and is expected to enroll 1000 unvaccinated subjects of 18-45 years of age.

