9vHPV will not have any effect on the elimination of the HPV infection already present or the production of new viral particles. However, the detection of HPV DNA and virions before and after vaccination is essential to identify women showing spontaneous viral clearance or latent or non-productive infection and distinguish these effects from the infectivity neutralization induced after vaccination. Differences associated with anatomical location, viral exposition, antibody availability and viral replication are characteristics that can be reflected in the analysis of cervical, anal, urine, vulvar and oral samples.

The proof of concept developed in this study is essential to generate scientific evidence that endorses vaccination in adult individuals. Although this study is focused on HPV-positive women, laboratory working methods and results obtained in oral and anal samples could be the basis for a future study on HPV-positive men, also a silent reservoir for HPV infection. Results may be not only determinant in designing more effective population-based vaccination programs following the 2018 World Health Organization recommendations for cervical cancer elimination, but also have an impact on the incidence of non-cervical anogenital and oropharyngeal cancers in both men and women.

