| 
Hypothesis. 9vHPV promotes the production and exudation of anti-HPV antibodies, which neutralize new HPV16/18 virions and reduce the infective capacity of body fluids in HPV-positive women and the transmission of HPV infection.
                                                                                                                                                                                                                                                 | 
 
● Detection of HPV 6/11/16/18/31/33/45/52/58 L1 antibodies in cervical, anal, urine, vulvar and oral samples collected before and after 9vHPV vaccination, using             
 
– ELISA for types 16 and 18 in samples from RIFT-HPV 1 and 2 study cohorts,
 
– cLIA for all 9vHPV-covered types samples from RIFT-HPV 1 study cohort.
 
 
 
 
This endpoint will allow to associate the reduction in viral infectivity with the presence of neutralizing antibodies.
 
 
● HPV16/18 virion detection (using ELISA, electronic microscopy) and HPV DNA detection and genotyping (using Anyplex HPV28) in cervical, anal, urine, vulvar and oral samples collected before and after 9vHPV vaccination.
 
 
This endpoint will allow to identify samples of subjects with a non-productive viral infection or undergoing natural clearance, and distinguish them from samples of subjects with productive but reduced infection due to 9vHPV vaccination.
 |

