#### **8.2.2.2 HPV Test and Genotyping (Anyplex HPV28)**

The Anyplex II HPV28 (Seegene, Inc) will be used for detection and genotyping of HPV DNA in cervical, anal, urine, vulvar and oral samples from the study subjects. The purpose of the test is to distinguish reduction of infectivity due to 9vHPV vaccination from spontaneous clearance of the HPV infection.

Anyplex II HPV28 is a semi-quantitative method based on real-time PCR able to detect and identify 19 high risk-HPV types (16, 18, 26, 31, 33, 35, 39, 45, 51, 52, 53, 56, 58, 59, 66, 68, 69, 73, 82) and 9 lower risk-HPV types (6, 11, 40, 42, 43, 44, 54, 61, 70) with high sensitivity and specificity.

Samples will be subjected to DNA isolation prior to Anyplex II HPV28 assays with automated Maxwell® RSC Tissue DNA Kit (Promega) according to manufacturer instructions. The genotyping assay comprises multiplex real-time PCR reactions with type-specific primers and probes for the detection of all mentioned HPV types. The type-specific probes are each labelled with a different fluorescent label, and the fluorescent emission is captured by the CFX96 thermal cycler (BioRad). Fluorescent signal intensity correlates with the abundance of the target DNA and a Ct value is assigned according to the cycle in which fluorescent signal exceeds a threshold. Positivity for a given HPV type will be considered when Ct<35. Human beta-globin will also be analyzed as internal control of cellularity.

The Anyplex II HPV28 is a validated method and currently in use for clinical diagnosis.

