##### 9.1.1.1.2 *Inclusion in the analysis population*

The below criteria will be followed to include cases in the analysis population:

Before vaccination (Visit 1):

- HPV16/18/16+18 positive DNA detection and genotyping (using Anyplex HPV28) in collected cervical, anal, urine, vulvar and oral samples.
- HPV16/18 positive virion detection (using ELISA, electronic microscopy) in collected cervical, anal, urine, vulvar and oral samples.

Therefore, cases showing:

- negative HPV16/18 DNA test and/or
- absence of HPV16/18 viral particles,

will not be included in the analysis population.

After vaccination (Visits 2 to 4, Months 2, 6 and 7):

- HPV16/18/16+18 positive DNA detection and genotyping (using Anyplex HPV28) in collected cervical, anal, urine, vulvar and oral samples.
- HPV16/18 positive virion detection (using ELISA, electronic microscopy) in collected cervical, anal, urine, vulvar and oral samples.
- Positive detection of exudated HPV 6/11/16/18/31/33/45/52/58 L1 antibodies in collected cervical, anal, urine, vulvar and oral samples.
- Positive detection/titration of HPV 6/11/16/18/31/33/45/52/58 L1 antibodies in collected serum samples (positive seroconversion).

Therefore, cases showing:

- negative HPV16/18 DNA test and/or
- absence of HPV16/18 viral particles and/or

- absence of exudated HPV L1 antibodies and/or
- absence of positive seroconversion,

will not be included in the analysis population.

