## 9.2 Sample Size and Power

### 9.2.1 RIFT-HPV 1 cohort

The sample size for this cohort has been calculated based on the demonstration of viral infectivity reduction before and after a 3-dose regimen of 9vHPV vaccination in cervical samples as a reference.

Accepting an alpha risk of 0.05 and a beta risk of less than 0.2 in a bilateral contrast, it has been estimated that a minimum of 39 women fulfilling the 3-dose vaccination schedule is needed to detect a difference equal to or greater than a 25% infectivity reduction in cervical samples.

It has been estimated a 40% sampling loss from those study subjects:

- showing an HPV16/18/double 16-18 positive result not confirmed by Anyplex HPV28,
- not fulfilling the 9vHPV 3-dose schedule,
- showing HPV clearance at Month 7 visit,
- showing a non-productive infection before vaccination.

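### A negative DNA or virion test after vaccination cannot show its cause in a single-arm study, so the primary exclusion rule may discard part of a vaccine effect and cannot do the separating job claimed for it

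*Protocol*

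**What the plan says.** Section 9.1.1.1.2 sets the analysis population for the primary objective. At Visits 2 to 4, a case is left out if it shows a "negative HPV16/18 DNA test and/or" no viral particles (antibody conditions follow, which are not at issue here). Section 9.2.1 counts clearance at Month 7 as sampling loss.

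The protocol says what these tests are for. Section 8.2.2.2, on the DNA test: "The purpose of the test is to distinguish reduction of infectivity due to 9vHPV vaccination from spontaneous clearance of the HPV infection". Section 3, repeated in 1.1.5, says the DNA and virion endpoint identifies non-productive infection or natural clearance and will "distinguish them from samples of subjects with productive but reduced infection due to 9vHPV vaccination". Section 8.2.2.4 makes a parallel claim for virion detection and non-productive infection.

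The premise is in Section 2.1: "9vHPV will not have any effect on the elimination of the HPV infection already present or the production of new viral particles". Section 2.2.6 then reports, from an observational cohort of couples, that "vaccinated women with infections of HPV types covered by the vaccine (acquired prior to vaccination) had lower viral loads than unvaccinated women".

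The study has no control group (Sections 1.2.1 and 4.1). DNA positivity is a quantity threshold, Ct below 35 (Section 8.2.2.2).

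**The concern.** Membership of the primary set depends on a result measured after treatment. That is harmless to the vaccine comparison only if treatment cannot change the result. Section 2.1 says it cannot; the evidence cited in Section 2.2.6 leaves room for doubt. If vaccination lowers viral load, some women cross the Ct cut-off, or become virion-negative, because of the vaccine. They are then removed as though they had cleared the infection naturally.

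At stake is what the primary result means. It describes women still DNA- and virion-positive after vaccination, but it would be read as the vaccine's effect with natural clearance taken out. The specified sensitivity analyses do not test this. Section 9.1.1.2 restricts to women seronegative before vaccination, and Section 9.1.3 uses questionnaire data when necessary. Neither brings the excluded women back.

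**Working it through.** **1. The plan's own figure.** Section 9.2.1 states that "a minimum of 39 women fulfilling the 3-dose vaccination schedule is needed" for a 25% reduction, two-sided alpha 0.05, power 80%. By the paired normal approximation, n = (1.960 + 0.842)² × (SD/d)² = 7.849 × (SD/d)². No SD is given, so 39 cannot be reproduced. Back-solving, SD = 0.25 × √(39/7.849) = 0.557. The 25% is used below only as an effect size for illustration.

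**2. The logic.**
- Section 2.1: no effect on existing infection or on particle production. If true, the vaccine causes no exclusions.
- Section 2.2.6: lower load in vaccinated women with earlier vaccine-type infection. If part of this is a vaccine effect, the vaccine can cause exclusions.
- Section 8.2.2.2: the test registers whether DNA crosses a threshold. Natural and vaccine-related falls look the same.
- Section 4.1: no unvaccinated women from whom to estimate the natural rate of turning negative.

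The tests can therefore identify undetectable virus, but not its cause.

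**3. Illustration. Every input is assumed.** Log10 virus relative to the detection limit: Visit 1 is L1 = S + e1; Visit 4 is L4 = S − v − w + e4. S ~ N(m, 0.8) with m = 0.5, 1.0 or 1.5; e1 and e4 ~ N(0, 0.35). The vaccine's load effect is v ~ N(0.125, 0.35) for a 25% fall (−log10 0.75 = 0.125), N(0.301, 0.35) for 50%, and 0 for none. Natural decline w is 0 unless stated. The planned set needs L1 > 0 and L4 > 0; the wider set needs only L1 > 0. The result is the fall implied by the median log change, over the three values of m, with simulation and rounding error of about one point.

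| Assumed truth | Planned set | All positive at Visit 1 |
|---|---|---|
| No effect, no decline | 0% | 3–14% |
| 25% fall, all through load | 12–21% | 27–36% |
| 50% fall, all through load | 35–45% | 52–57% |
| 25% neutralisation, load unchanged | about 25% | 27–36% |
| No effect; 30% of women decline naturally by 0–2 log10 | about 14–24% | 37–44% |
| No effect; 50% decline naturally by 0–1.5 log10 | 28–43% | not tabulated |
| 25% fall through load, plus 30% declining by 0–2 log10 | 24–40% | 55–61% |

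The wider-set entry for neutralisation follows from the first row: 1 − 0.75 × 0.97 = 27% and 1 − 0.75 × 0.86 = 36%. The 3–14% with no effect is regression to the mean from requiring positivity at Visit 1.

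**4. How many women the vaccine could remove.** A second assumed model has log10 load N(1,1) or N(2,1), restricted to detectable at Visit 1, with visit noise SD 0.5 and no natural clearance. Load effects of 0.1, 0.25, 0.5 and 1.0 log10 remove an extra 2.1, 5.8, 13.7 and 33.4% of women (lower load), or 0.7, 1.9, 4.9 and 14.6% (higher load). With no load effect the figure is 0.

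**The case against.** The best defence is that the protocol's hypothesis is neutralisation of released virions, not clearance. Sections 2.1 and 2.2.4 both say antibodies do not suppress virus production. The evidence in Section 2.2.6 is a between-group comparison in an observational cohort. It is not a before-and-after change, it carries no size, and a lower load is not an undetectable one. Section 3's wording on vaccine-reduced infection describes women who are still productive, whom the virion rule keeps. All of this stands. It is why the rule *may* discard vaccine effect, not why it does.

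Dropping the rule would not solve the problem either. Without controls, natural clearance would then be credited to the vaccine. That stands too, and argues for keeping the planned set.

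The protocol also lists DNA and virion detection as endpoints and defines persistent infection (Section 9.1.4), so the numbers turning negative can be derived. What is missing is any analysis of infectivity in the excluded women.

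A reader might infer three stronger things, none of which the documents support:
- *The reported reduction must be too small.* Women who decline naturally but stay positive are retained, and their fall counts as vaccine effect.
- *The planned and wider sets bracket the truth.* With partial natural decline and no vaccine effect, both lie above it.
- *The planned set falls short of the 25% design effect.* That 25% is an infectivity reduction. It shrinks to 12–21% only if all of it is assumed to act through viral load.

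**Conclusion.** The point holds in a limited form. The protocol assigns the DNA and virion tests a property that they cannot have in a single-arm design, and it conditions the primary analysis on that property. Sections 2.1 and 2.2.6 are in tension and are not reconciled.

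The loss of vaccine effect through the rule is zero if the vaccine acts only by neutralisation and leaves load unchanged. If it lowers load, the loss grows with the size of that effect: 0.7 to 33.4% of women removed over an assumed 0.1 to 1.0 log10. The net bias in the estimate has no fixed direction, because retained natural decline pulls it upward. All sizes rest on assumed load distributions, since the protocol supplies none. The change is worth making because it alters what the primary result can be said to show, but it does not invalidate the planned analysis.

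**What to change.** - Reconcile the premise in Section 2.1 with the evidence cited in Section 2.2.6.
- Keep the planned set, and describe it as *women still DNA- and virion-positive after vaccination*.
- Add a labelled supportive signed-rank analysis for each sample type. Include all women DNA- and virion-positive at Visit 1 and use measured Visit 4 infectivity whatever the later DNA or virion result.
- Present the two as analyses with different stated biases, not as lower and upper bounds. The planned set can lose vaccine effect and retains partial natural decline. The wider set includes natural clearance and regression to the mean.
- Report how many women turn DNA-negative or virion-negative, by visit and sample site.
- In Sections 1.1.5, 2.1, 3, 8.2.2.2 and 8.2.2.4, replace the claim that the tests separate vaccine effect from clearance or non-productive infection with *identify women with no detectable virus, cause undetermined*.

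The cost is one extra test per sample type, a table of counts and wording in five places. The schedule of activities already has the infectivity assay at every visit, so no samples are added. The small downside is that the supportive analysis mixes in natural clearance and must say so wherever it is reported.
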